#### Secondary outcomes of the study

The secondary outcomes (estimates of effect size for the main trial) will be the following:Percentage of included women who:Delivered in an appropriate place, as recommended by the health worker according to their level of riskDied (maternal death)Suffered serious maternal morbidityTook up postpartum family planning: LARC vs other methods and within 48 h/by 6 weeks/by 6 months/by 12 monthsPercentage of women who initiated PPFP who are still using it: at 6 months and at 12 monthsPercentage of babies born to included women/couples who:Were live born vs stillborn (fresh/macerated)Died within 7 days, 28 days or 12 months of birthHad a serious illness (for example requiring hospital admission/causing long-term complications) within 7 days, 28 days or 12 months of birthLost a sibling during the 12-month follow-up period

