#### Training health workers

Health workers at the intervention health centre IIIs will be invited to attend a 6-day refresher training on general communication skills, couples’ counselling, information and practical skills for antenatal risk assessment, birth preparedness and postpartum contraception provision (see Table 3). Health workers will be asked to provide couples’ counselling to couples who come together to the antenatal clinic.

**Table 3 Tab3:** Training schedule for health workers

Time	Day 1	Day 2	Day 3	Day 4	Day 5	Day 6
8:30–9:00 am	Registration and introductions	Recap	Recap	Recap	Recap	Recap
9:00–9:30 am	Pre-course questionnaire	High-risk pregnancies	Implant—insertion (including practice on models)	Participants practice insertion and removal of IUD on models	21: gender-based violence and role-plays	Clinical practicum
9:30–10:00 am	Introduction to the ACCU project and this course	Birth planning				
10:00–10:30 am	General counselling skills	Role-plays on birth planning and couples’ counselling	Implant—follow-up, management of side effects			
Health break						
11:00–11:30 am	The REDI counselling framework	Role plays on birth planning and couples’ counselling	Implant removal	Clinical practicum	Clinical practicum	21: records management
11:30 am 12:00 nn	Couples’ counselling skills and self-awareness exercise	Postpartum family planning and concepts	Practice implant removal on models			
12:00–1:00 pm		Barriers to uptake of PPFP	PPIUD assessment			Post-course questionnaire
Lunch						
2:00–3:00 pm	Role-play—practice	PPFP methods overview	Role-play—practice	Clinical practicum	Clinical practicum	Feedback on the course questionnaire
3:00–4:00 pm	Forming alliances and directing communication; 6: mediation skills	Implant—assessment and role-play	PPIUD insertion	Role-play practice	Feedback and discussion on lessons learnt from clinical practicum and challenges	Post-course evaluation ACCU study administration Closure
4:00–4:50 pm	Solution-focussed model of couples’ counselling	Health education and films	PPIUD follow-up, removal, post-insertion care			
4:50–5:00 pm	Daily evaluation					

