**Assessments**						
***Relevant demographics, medical/obstetric history***		X				
***Plans for birth and PPFP***		X	X			
***Use of antenatal clinic, delivery outcomes***				X		
***Use of PPFP***				X	X	X
***Maternal and child survival outcomes***				X	X	X

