### Outcomes

#### Primary process/feasibility outcomes

The following will be the primary feasibility outcomes:Percentage of eligible women who consent to participate and are recruitedPercentage of included women who:Can be followed up and provide outcome data on place of delivery and uptake of family planning: to 1 week postpartum, to 6 months postpartum and to 1 year postpartum.Whose partners agreed to participate in the projectReceived individual counselling from the VHT: on one or more occasions and at each study visitReceived couples counselling from the VHT on one or more occasionsAttended the antenatal clinic at the health centre one or more timesAttended the antenatal clinic at the health centre with their partner one or more timesReceived individual counselling at the antenatal clinic on PPFPReceived individual counselling at the antenatal clinic on birth planningReceived couples’ counselling at the antenatal clinic on PPFPReceived couples’ counselling at the antenatal clinic on birth planningWere given correct advice on the recommended place of delivery (according to their level of risk)Watched the health education films: with the VHT and at the antenatal clinicPercentage of included couples who:Were offered and attended antenatal clinics and counselling at weekendsWere counselled and consented for long-acting reversible methods of PPFPProportion of women/couples attending antenatal clinic who were offered counselling on both birth planning and use of long-acting reversible methods of PPFP at the same visitProportion of women/couples counselled who agreed on PPFP in a single session and proportion of women/couples counselled who agreed after attending extra sessionsPercentage of working days when the films on family planning are screened in antenatal clinics (in intervention areas)Percentage of VHT visits when:Counselling was delivered to the woman/couple about birth planning/family planningData was correctly entered directly into the COSMOS app on the smartphoneCosts of intervention/control—health economics

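### Appropriate place of delivery is scored against advice that the intervention changes in one arm only, so the same delivery can be scored differently by arm

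*Protocol article*

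**What the plan says.** Under Secondary outcomes of the study, the Protocol article counts women who delivered "in an appropriate place, as recommended by the health worker", with a closing qualifier that ties the recommendation to the woman's level of risk. The denominator is all included women: "Percentage of included women who:Delivered in an appropriate place". The list opens by stating its purpose: "The secondary outcomes (estimates of effect size for the main trial) will be the following".

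The intervention acts on the person who makes that recommendation. Under Training health workers: "Health workers at the intervention health centre IIIs will be invited to attend a 6-day refresher training", and the content includes "information and practical skills for antenatal risk assessment, birth preparedness and postpartum contraception provision". Under Training VHTs, only village health teams in intervention areas are trained to recognise high-risk pregnancies, to promote delivery in a place suited to risk, and to send couples to the clinic. Control areas receive Ministry of Health usual care (Abstract, Methods).

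Under Primary process/feasibility outcomes, a separate item is whether women were "given correct advice on the recommended place of delivery", again judged by risk level.

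**The concern.** An outcome compared between arms needs a yardstick that means the same thing in both. Here the yardstick is advice given after randomisation, by staff whom one arm retrains to give it. If a health worker misses a risk and advises the health centre, a woman who delivers there meets the outcome as written. If a retrained worker recognises the same risk and advises a different place, a woman who delivers at that same health centre does not. Risk and delivery are the same, but the score is not.

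A second route concerns women who receive no recommendation. Clinic attendance and counselling are themselves promoted by the intervention, so such women may be commoner in control. They remain in the denominator, and the article gives no separate rule for them. The natural reading is that they do not meet the outcome.

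Place of delivery is one of the two avoidable factors that the Discussion part of the Abstract says the intervention addresses. A distorted estimate here would feed the planning of the full trial, and the definition itself might be carried over. Advice quality is also a property of the health centre, which is the unit of randomisation. A centre-specific yardstick could therefore disturb the intra-cluster correlation that the Statistical analysis plan section intends to estimate.

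**Working it through.** **The plan's own figure.** The only sample-size figure is the recruitment target: 4 areas × 10 village health teams × 35 women = 1400, or 700 per arm. It reproduces, and the point does not depend on it. The article gives no rates for risk, advice or place of delivery, so every rate below is an assumption.

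**Set-up.** Both arms have the same risk mix and the same places of delivery, so a sound outcome must show a difference of 0. Only the advice differs. For illustration, the risk standard is taken to send high-risk women to a higher-level facility, and a high-risk woman whose risk is missed is advised to use the health centre. This is not a statement of what the clinical rule should be.

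**Step 1: high-risk women only, all delivering at one of the two places.** Let q be the share at the higher-level facility and s the share whose risk is recognised, with s = 0.5 in control and 0.9 in intervention. The score against advice is s·q + (1 − s)(1 − q). The score against risk is q in both arms.

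| q | Control | Intervention | Difference |
|---|---|---|---|
| 0.40 | 0.5×0.40 + 0.5×0.60 = 0.50 | 0.9×0.40 + 0.1×0.60 = 0.42 | -8 points |
| 0.50 | 0.5×0.50 + 0.5×0.50 = 0.50 | 0.9×0.50 + 0.1×0.50 = 0.50 | 0 |
| 0.60 | 0.5×0.60 + 0.5×0.40 = 0.50 | 0.9×0.60 + 0.1×0.40 = 0.58 | +8 points |

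The sign depends on q. If 20% to 40% of women are high-risk and advice to the rest is equal, 8 points among high-risk women become 8 × 0.2 = 1.6 to 8 × 0.4 = 3.2 points over all women.

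**Step 2: all women, some delivering elsewhere.** Let h be the high-risk share (0.20 to 0.40). Among high-risk women, q deliver at the higher-level facility and c at the health centre, with (q, c) = (0.30, 0.50) or (0.50, 0.30); the other 20% deliver elsewhere. Recognition is 0.30 to 0.70 in control and 0.90 in intervention. Low-risk women contribute (1 − h) × 0.70 in each arm, which cancels.

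- Exact match to advice required: difference = h × (0.90 − s_control) × (q − c). Extremes: 0.40 × 0.60 × (−0.20) = -4.8 points and 0.40 × 0.60 × 0.20 = +4.8 points.
- A higher level than advised also counts: difference = −h × (0.90 − s_control) × c. Extremes: −0.40 × 0.60 × 0.50 = -12.0 points and −0.20 × 0.20 × 0.30 = -1.2 points.

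**Step 3: no recommendation, counted as failure.** Let r be the share given a recommendation (0.50 to 0.80 in control, 0.90 in intervention) and p the share of advised women whose delivery matches it (0.50 to 0.70). Difference = (0.90 − r_control) × p. Extremes: 0.10 × 0.50 = +5 points and 0.40 × 0.70 = +28 points.

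**Step 4: one common standard.** Identical risks and deliveries give identical scores, so the difference is 0 in every scenario above.

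**The case against.** The strongest reply is that the outcome was meant to be risk-based. Its definition ends by referring to level of risk, the Training VHTs section describes an appropriate place by risk without mentioning anyone's advice, and the item on correct advice presupposes a risk standard. The detailed scoring rule may stand in the full protocol or the questionnaires, which are not shown. This lowers confidence about intent. It does not remove the words that make the health worker's recommendation the criterion, and listing correctness as a separate outcome shows that advice and standard are two different things. The point is about a rule that is stated, not about missing detail.

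Three stronger readings are tempting, and the article does not support them:

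- A reader might infer that identical deliveries will always be scored differently. Only women whose advice differs by arm, or who receive none, are affected.
- A reader might infer that the outcome is biased against the intervention. Step 1 shows the artefact vanishing at q = 0.50 and reversing at 0.60, and Step 3 favours the intervention throughout.
- A reader might infer that unadvised women cannot be scored or drop out selectively. The denominator is already all included women. Eligibility also requires that a woman plans to attend the study clinic, which may keep their number small, although attendance is itself measured and so not taken for granted.

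Finally, this is one secondary outcome in a four-cluster feasibility trial whose primary analysis concerns feasibility. The specific objectives seek to quantify a change only for postpartum family planning, and two clusters per arm will give a very imprecise difference in any case. All of that stands, and it limits the severity.

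**Conclusion.** The point holds in this form: the outcome is measured against a post-randomisation recommendation that the intervention is designed to change in one arm, so women with the same risk and the same place of delivery can be scored differently by arm. The mechanism follows from the article's text alone.

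Its size does not. Over the assumed ranges the spurious difference is -4.8 to +4.8 points with exact matching, -12.0 to -1.2 points if a higher level also counts, and +5 to +28 points if unadvised women count as failures. The wrong-advice and no-advice routes were calculated separately and may offset each other. An unknown sign makes the estimate harder to interpret, not safer.

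No feasibility conclusion changes. The damage is confined to an estimate, and possibly a definition, passed on to the main trial. This is a should-fix, not a must-fix.

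**What to change.** Redefine the outcome as the percentage of included women whose place of delivery agrees with the place assigned to their risk level by one pre-set classification, applied in the same way to both arms. It should be the same standard that the correct-advice outcome already needs. Its clinical content is for the investigators. State whether agreement means an exact match, since Step 2 shows that this matters. Derive the classification without sight of arm from the item listed in Table 4 as "Relevant demographics, medical/obstetric history". Keep all included women in the denominator, as now. Report delivery where advised separately, as an adherence measure, with the number of women given no recommendation in each arm.

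The cost is one redefined outcome and one derivation. Baseline history and place of delivery are collected in both arms, so the visit schedule need not change. Two limits apply. Table 4 schedules the history at baseline only, and the Follow-up visits section confines the second antenatal visit to clinic use and intentions. Risks that arise after baseline would therefore be missed unless they are already recorded in both arms. The baseline questionnaire (Additional file 3) is not shown and must be checked to confirm that it supports the classification. Recruitment had already started (Status of the study), so any gap in it could not be filled in the same way for women already enrolled.

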**Methods:**

This is a two-group, non-blinded cluster-randomised controlled feasibility trial of a complex intervention. Primary health centres in Uganda will be randomised to receive the intervention or usual care provided by the Ministry of Health. The intervention consists of training village health teams to provide basic counselling to couples at home, encouraging men to accompany their wives to an antenatal clinic, and secondly of training health workers to provide information and counselling to couples at antenatal clinics, to facilitate shared decision-making on the most appropriate place of delivery, and postpartum contraception. We aim to recruit 2 health centres in each arm, each with 10 village health teams, each of whom will aim to recruit 35 pregnant women (a total of 700 women per arm). The village health teams will follow up and collect data on pregnant women in the community up to 12 months after delivery and will directly enter the data using the COSMOS software on a smartphone.

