### Sample size

There are four clusters—two intervention and two control areas—in the feasibility trial. In each of these areas, we will engage 10 VHTs to recruit participants. Each VHT will aim to recruit 35 women over a 6-month period, so in total, we will aim to recruit about 1400 women. A formal sample size calculation is not required for a feasibility study, but a sample of this size will allow us to estimate the key parameters for a future full-scale trial, including the variability, clustering and retention rate.

For the process evaluation, we will use a “purposive” sampling approach to select respondents (according to socio-demographic and organisational factors expected to influence the delivery or effectiveness of the intervention). We plan six separate FGDs, each of six to ten participants, two each for the following categories of individuals: (a) postpartum women—the age will determine their allocation to subgroups: adolescent girls (≤ 20 years), women 21 years and above; (b) men who are partners or husbands of women who deliver during the study; and (c) VHTs involved in the study. We will conduct about 20–30 in-depth interviews with clinic managers, health service providers, VHTs and couples. We will interview postpartum women and their partners, who took up, and who did not take up, the offer of couples’ counselling at home and at ANC and the offer of a contraceptive method, in order to understand the factors influencing their decisions, their experience of the intervention and their suggestions for improving it. We will also ask about the degree of contamination between study areas and will assess this as a feasibility outcome.

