### Cost effectiveness

Quantitative data on the role of costs both formal and informal in relation to the intervention will help in the design of a cost-effectiveness study. The cost-effectiveness of the intervention versus control depends on the additional cost of the intervention plus any knock-on effects on other costs. In this feasibility stage, both of these will be explored. We will evaluate the different ways of delivering the intervention in relation to its cost, given that the method of delivery may have to vary by place. The standard questionnaires will include questions about the costs of different components of care in both groups. The aim will be to assess in the process evaluation the likely cost of the intervention if delivered in different ways and to guide how it might be delivered most efficiently in the main trial. The knock-on effects of such an intervention, which may be diffuse (such as travel to the venue, time off work and cost of measures to encourage spouse attendance) will also be explored qualitatively in the process evaluation. We will also explore in an open-ended way what other non-healthcare costs might be incurred by trial participants. One perspective often adopted for costing is that of the health care provider, and this will be a perspective included in the main trial.

Cost per birth averted is likely to be the measure of cost-effectiveness in the main trial but the appropriateness of this will also be explored particularly with the local health service leaders and taking account of other relevant work in the field and in terms of policy alternatives. Cost per quality-adjusted life year (QALY) is not usually seen as appropriate for interventions to do with fertility control. Thus, consideration will be given to the inclusion of other secondary outcomes by use of an impact inventory which will list all the effects, both to do with outcomes and resource use, of the intervention. The eventual cost-effectiveness analysis will compare the results from the trial with those in the relevant literature.

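### PPFP continuation is taken among initiators only, so its arm difference is not a randomised effect size, and no listed outcome gives use at 6 and 12 months among all included women

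*Protocol article*

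**What the plan says.** The protocol article, under Secondary outcomes of the study, introduces the list with "The secondary outcomes (estimates of effect size for the main trial) will be the following". Two entries concern PPFP use:

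- Uptake, as a percentage of included women, classified as "LARC vs other methods and within 48 h/by 6 weeks/by 6 months/by 12" months. This is cumulative: once a woman has started, she counts at every later time point.
- Continuation, as the percentage "of women who initiated PPFP who are still using it" at 6 and at 12 months. The denominator is initiators. The text does not say by when a woman must have started to enter it.

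No primary or secondary outcome is the percentage of all included women using a method at 6 or 12 months. The schedule in Table 4 does record PPFP use at all three postnatal visits (1 week, 6 months and 12 months). Objective 3 is worded in terms of uptake. The Statistical analysis plan section intends to estimate the variance of the proposed outcome measures and the ICC at health-centre and VHT level. The Cost effectiveness section adds: "Cost per birth averted is likely to be the measure of cost-effectiveness in the main trial".

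**The concern.** An effect size needs the same kind of women in the denominator of both arms. Initiators do not meet that condition. Starting a method happens after randomisation, and raising the number who start is the purpose of the counselling. If the intervention draws in women who are less committed to a method, continuation falls in the intervention arm even when no woman is worse off.

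Without an initiation window, the continuation figure also pools women who started within 48 hours of delivery with women who started shortly before the visit, for whom still using is close to automatic. The mix of the two may differ between arms.

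Uptake has the proper denominator but counts women who stopped within weeks. The two outcomes can therefore point in opposite directions, and no listed outcome resolves which way actual use has moved. That quantity bears most directly on the stated rationale (closely spaced pregnancies in the first year postpartum) and on births averted.

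**Working it through.** **The plan's own figures.** From Sample size: "There are four clusters"; in each, "we will engage 10 VHTs to recruit participants"; "Each VHT will aim to recruit 35 women over a 6-month period". So 4 × 10 × 35 = 1,400 women, and 2 × 10 × 35 = 700 per arm, which agrees with "a total of 700 women per arm" in the abstract. The article gives no expected uptake or continuation for the trial arms, so every rate below is an assumption.

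**Identity.** Use at time t among all women = (uptake by t) × (share of those initiators still using at t).

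**Selection alone can reverse the sign.** Suppose 40% would start in either arm and 80% of them continue. The intervention adds a further 15% who start, of whom 40% continue.

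- Control: uptake 40%; continuation 80%; use 0.40 × 0.80 = 32.0% (224 of 700).
- Intervention: uptake 55%; use 0.40 × 0.80 + 0.15 × 0.40 = 0.32 + 0.06 = 38.0% (266 of 700); continuation 0.38 / 0.55 = 69.1%.
- Differences: uptake +15 points, continuation −10.9 points, use +6.0 points. No woman's continuation was harmed.

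**Range.** Control as above (40%, 80%, use 32.0%); intervention uptake 55%.

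| Intervention continuation | Use among all women | Difference in use |
|---|---|---|
| 70% | 0.55 × 0.70 = 38.5% | +6.5 points |
| 58% | 0.55 × 0.58 = 31.9% | −0.1 points |
| 50% | 0.55 × 0.50 = 27.5% | −4.5 points |

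Uptake shows +15 points in every row. The break-even continuation is 0.32 / 0.55 = 58.2%.

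**Can use be recovered from the two listed outcomes?** Only if their windows match. Suppose 40% start by 6 months and 70% of them are using at 12 months; a further 10% start later and 95% of them are using at 12 months. True 12-month use is 0.40 × 0.70 + 0.10 × 0.95 = 37.5%. With all initiators by 12 months as denominator, continuation is 0.375 / 0.50 = 75%, and 0.50 × 0.75 = 37.5%, which is correct. If continuation covers only those who started by 6 months, the product is 0.50 × 0.70 = 35.0%, which is 2.5 points low. Nor does multiplying two percentages yield an ICC for use.

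**What planning on uptake alone could cost.** Required size is proportional to [p1(1−p1) + p2(1−p2)] / (p1−p2)², assuming the same design effect for both outcomes. For uptake of 40% against 60%: 0.48 / 0.20² = 12.0.

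- Continuation 75% in both arms: use 30% against 45%; 0.4575 / 0.15² = 20.3; ratio about 1.7.
- Continuation 75% against 60%: use 30% against 36%; 0.4404 / 0.06² = 122.3; ratio about 10.

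**The case against.** The strongest reply is that this is a missing reporting line and not a flaw in design or data. PPFP use is scheduled at 6 and 12 months, so current use can be derived; it is also the product of the two listed outcomes when their denominators agree. Continuation among starters is a legitimate descriptive measure, and no section specifies a test or model comparing it between arms. Uptake is recorded by time window, so early and late starters could be separated. The Statistical analysis plan section says that its variance and ICC estimates will not suffice alone for a future calculation, and nothing fixes the main trial's primary outcome.

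Most of that stands, and it limits the weight of the point. It does not remove it: the list gives its own purpose as effect sizes for the main trial, continuation cannot serve that purpose, and the text does not guarantee matching windows.

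A reader might go further and infer any of the following, which the article does not support:

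- That a main trial would be about ten times too small. That ratio needs an assumed fall in continuation; with equal continuation it is about 1.7. The article does not say that the main trial will be powered on uptake.
- That neither outcome can inform cost per birth averted. Together they give current use when the windows match, and the article calls that measure only likely, with its suitability still to be explored.
- That uptake is the wrong outcome. Objective 3 is about uptake, so demoting it would be a preference.
- That a new pregnancy question is needed. The questionnaires are not shown, so whether one exists cannot be checked.

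**Conclusion.** The point holds as a gap in outcome definition. As listed, continuation is offered as an effect-size estimate although it is conditioned on a post-randomisation event and has no initiation window. Its arm difference can be biased or reversed in sign relative to actual use: 69% against 80% for continuation alongside 38% against 32% for use in the assumed example. With uptake fixed at +15 points, the assumed scenarios put the difference in use anywhere from +6.5 to −4.5 points.

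The possibility of reversal follows from the definitions; its size rests wholly on assumed rates. With two clusters per arm any arm difference will be imprecise, so the issue is which quantity is carried forward and not how precisely it is estimated. The consequence falls on the planning of the main trial and does not undermine the feasibility aims.

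**What to change.** - Add a secondary outcome: the percentage of all included women followed up who are using PPFP (LARC / other) at the 6-month and at the 12-month visit, by arm, with its ICC at the levels already planned. Show it beside the retention figures, since loss to follow-up affects its denominator.
- Keep cumulative uptake as listed; it answers objective 3.
- For continuation, state by when a woman must have started to be counted, and report it descriptively and not as an effect-size estimate.
- If the questionnaires already record a new pregnancy since the index delivery, list it as an outcome.

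The cost is wording and one derived variable. The continuation outcome already requires knowing who is using a method at 6 and 12 months, and women who never started are non-users, so no new item is needed. Follow-up was under way when the article was written, and protocol modifications need prior ethics approval, so the change should be submitted as an amendment to the outcome definitions.
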